### MRI data analysis

An fMRI data processing assistant based on statistical parameter mapping will be used to preprocess the original MRI data (DPARSF, http://rfmri.org/DPARSF) using MATLAB R2015b. After complete preprocessing, data processing and analysis of brain imaging of the amplitude of low-frequency fluctuation (ALFF) will be processed by the resting-state fMRI data analysis toolkit [22]. Afterwards, a comparison, correction and acquisition of the image will be executed via the Rest Slice Viewer software, and the final result will be presented in combination with the specific anatomical position of the corresponding area of MNI coordinates.

The results of fMRI will be interpreted by two different radiologists, and then the rehabilitation doctors will further analyse this in combination with clinical symptoms. Finally, the two doctors will reach a final interpretation through consultation.

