**Methods:**

This clinical research will be a randomised, blind, sham-controlled trial. Thirty-six patients with PDM will be randomly divided into the rESWT group (*n* = 18) and the sham rESWT group (*n* = 18). In the rESWT group, treatment will be applied once within 48 h of menstruation at six abdominal myofascial trigger points. The sham rESWT group will receive sham shockwave therapy on the same sites but without energy input. Other dysmenorrhoea-related treatments in both groups will be limited. The main indicators include the short form of the McGill Pain Questionnaire and the Cox Menstrual Symptom Scale. The secondary indicators include the Zung Self-rating Anxiety Scale and Self-rating Depression Scale and functional magnetic resonance imaging (fMRI) changes in brain regions. Results will be evaluated at the screening, at baseline, and before and after treatment, and adverse treatments will be examined. Inter- and intragroup analyses will be performed.

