### Randomisation, concealment of allocation and blinding

Participants who meet the inclusion criteria will sign the informed consent form voluntarily and will be eligible for randomisation. They will be assigned randomly to the rESWT group or the sham rESWT group. The random sequence will be generated by a statistician using IBM® SPSS® statistics version 22.0 (IBM Institute, Inc., USA) who is not involved in the intervention or outcome evaluation.

The random number and group assignment will be sent immediately to the independent assessor by another research coordinator via an encrypted electronic file. As much as possible, evaluators will be prevented from communicating with the patients to avoid bias. This process will ensure that randomisation concealment will be competent and will be unaffected by the participants or practitioners.

It is not feasible for the therapist and the patient to be double blind because of the particularity of shock wave therapy. Before signing the informed consent form, patients will be told that they will receive shock wave treatment. Participants will not know their treatment allocation. The therapist will not be blinded, but will not assess the effectiveness of the treatment. Outcome assessors, data managers and statisticians will be blinded to treatment allocation. Prior to the start of the trial, all researchers will be trained to ensure the successful implementation of the blinding procedure.

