**Fig. 4 Fig4:**
[figure not shown]
Description of the shockwave instrument. Above is the front view of the shockwave instrument (model: MASTERPULS MP100), and below is the side view of the treatment handle (model: R-SW handpiece)

**Table 2 Tab2:** Details of rESWT intervention

Item	Detail	Description
rESWT rationale	Type of shock wave	Pneumatic ballistic extracorporeal shock wave therapy
	Reasoning for treatment	The best treatment option was selected according to our previous study results and other clinical trials of rESWT for primary dysmenorrhoea
	Extent to which treatment varies	None
Details of rESWT	Number of treatment sites per subject	6
	Names of points used	Attachment point of rectus abdominis above the symphysis pubis (bilateral) (blue dot in Fig. 3)
		Intersection of the anterior superior iliac spine with the outer margin of the rectus abdominis (bilateral) (yellow dot in Fig. 3)
		The anterior superior iliac spine shifts inward by approximately 2 cm along the line (bilateral) (location of the red dot in Fig. 3)
	Shock wave intensity	1.5–2.0 bar
	Shock wave frequency	10–14 Hz
	Number of hits from each site	600 times
	Response sought	None
Treatment regimen	Number of treatment sessions	1 time
	Treatment time	Within 48 h of menstruating
Other components of treatment	Details of other interventions administered to the rESWT group	None
	Setting and context of the treatment	Hospital rehabilitation section, outpatient department
Background of practitioner	Profile of the therapist	Specialist in rehabilitation medicine or a resident of more than 1 year under the guidance of the specialist in rehabilitation medicine
Control or comparator	Rationale for the control or comparator in the context of the research question	As a placebo control, a non-energetic sham rESWT was used

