This study aims to explore the differences in pain intensity, anxiety, depression, mood and functional brain networks in patients with PDM after rESWT treatment. To accurately elucidate the effect of rESWT, we will compare the changes in MRI indexes in the rESWT group and a sham rESWT group and test whether the changes in pain condition are related to changes in brain function after rESWT treatment. Although previous studies have examined brain function in patients with nervous disorders and abnormal change due to PDM, they only explored the disease itself and did not examine the intervention [23, 25, 26]. To our knowledge, our research will be the first to use MRI to reflect divergence of efficacy of rESWT treatment for PDM and the related neural mechanisms through a randomised controlled trial. Existing research [26] shows that midbrain activity is closely related to the Cox retrospective symptom scale (RSS; *r* = 0.489), and the medial prefrontal cortex activity and RSS showed negative correlation (*r* = −0.580); the medial prefrontal cortex aims to reduce the activity of the brain’s pain-regulating system. Thus, the CMSS was chosen as one of the main outcome measures for this study. This scale is usually employed to evaluate dysmenorrhoea symptoms and to detect the severity of dysmenorrhoea.

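### The fMRI group comparison is computed without readers, but its final interpretation follows a symptom-informed analysis and no numerical pain-brain analysis is given, so the conclusion for objective 2 can be steered by the clinical result

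*Protocol article*

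**What the plan says.** All references are to the protocol article. The Abstract lists "functional magnetic resonance imaging (fMRI) changes in brain regions" among the secondary indicators, and objective 2 is to explore the central mechanism of the treatment from resting fMRI.

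The section MRI data analysis describes software preprocessing, the ALFF calculation, and location of the results by MNI coordinates. It then describes a reading in three steps:

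1. "The results of fMRI will be interpreted by two different radiologists".
2. Next, "the rehabilitation doctors will further analyse this in combination with clinical symptoms".
3. "Finally, the two doctors will reach a final interpretation through consultation".

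The section Statistical analysis defines the group comparison: amplitude averaged over 0.01–0.08 Hz, two-sample t tests in SPM12 on the maps of the two groups, and p < 0.05.

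The Discussion states the aim to "test whether the changes in pain condition are related to changes in brain function" after treatment.

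On people and blinding, Table 2 gives the therapist's profile as "Specialist in rehabilitation medicine or a resident of more than 1 year under the guidance of the specialist in rehabilitation medicine". The section on randomisation, concealment and blinding says: "The therapist will not be blinded, but will not assess the effectiveness of the treatment". It also states that outcome assessors, data managers and statisticians are blinded. It does not name the radiologists or the rehabilitation doctors who take part in reading the fMRI results.

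**The concern.** Objective 2 asks what happens in the brain when pain is relieved. If imaging is to count as evidence on that question, it should be read without knowledge of the pain result. The plan instead brings the symptoms into the interpretation before it is final. The primary outcomes, SF-MPQ and CMSS, are themselves pain and symptom scales, so the reading is informed by the kind of information it is meant to be related to.

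A whole-brain map offers many regions on which to comment, and the article names none in advance. Readers who know the symptoms can stress the regions that fit and pass over those that do not. The Discussion adds weight to this step, because it expects MRI to identify treatment-specific pathways linked to pain relief even without a significant difference in effect.

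A second, smaller matter is who takes part. The rehabilitation doctors belong to the same discipline as the unblinded therapists, and the section on MRI data analysis does not say whether a treating doctor may join the consultation.

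**Working it through.** No arithmetic applies. The point depends on no sample size, error rate or effect size, and the article gives no figure to reproduce. The check sets the sections side by side.

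**Step 1. Does symptom information enter the computed endpoint?** The chain in MRI data analysis and Statistical analysis runs: preprocessing, ALFF per voxel, two-sample t tests on the two groups' maps, display on a standard image. No reader rating and no questionnaire score appears in it. Answer: no. The map would be the same whoever read it.

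**Step 2. Does it enter the interpretation?** MRI data analysis states that the rehabilitation doctors analyse the results with the clinical symptoms, and places this before the final consultation. Answer: yes, by the plan's own wording.

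**Step 3. Who settles the final interpretation?** Two doctors, by consultation. Three readings are open: the two radiologists, two rehabilitation doctors, or one of each. The radiologists are the only people counted as two earlier in that paragraph, so they are a natural reading. Under any of the three, the consultation comes after the symptom-informed step.

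**Step 4. Is the pain-brain relation analysed numerically anywhere?** The Discussion calls it something to be tested. Statistical analysis lists within-group tests, between-group tests and the two-sample t tests on maps. None relates ALFF change to score change. The only described step in which imaging and symptoms meet is the one in Step 2.

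**Step 5. Are the data for a numerical analysis available?** Yes. Table 1 places SF-MPQ, CMSS, SAS and SDS at both MRI visits, and Statistical analysis restricts the analysis to participants with both scans and both clinical evaluations. Each analysed participant, at most 36 (18 per group), therefore has an ALFF change and a score change.

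**Step 6. Does the blinding text cover the readers?** It bars the therapist from assessing effectiveness and blinds outcome assessors in general. Table 2 places the therapist in rehabilitation medicine. MRI data analysis gives rehabilitation doctors a part in the reading. No section says that these are different people, and none says that they are the same. Whether interpreting fMRI counts as assessing effectiveness is also left open.

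**Result.** Steps 1 and 2 place the weakness in the interpretation and not in the measurement. Steps 4 and 5 show that a numerical analysis could carry the pain-brain question, although the article describes only a consensus. Step 6 leaves an unresolved ambiguity.

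**The case against.** The strongest reply is that interpretation follows a finished statistical map. Symptoms can colour the account of significant clusters, but they cannot change ALFF values or t statistics. This stands in full. A reader might infer that the fMRI endpoint itself depends on the pain outcome; the document does not support that.

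A second reply is that bringing imaging and symptoms together is what the Discussion sets out to do, that nothing says reader opinion replaces ALFF values in that test, and that a condensed article may leave the correlation to an analysis plan. This stands in part. The missing correlation would not be a finding on its own, and the same holds for the multiplicity rule: a correction step is mentioned without detail, which may be given elsewhere. What remains is a procedure the article does state, in which the interpretation is agreed after symptoms have been consulted. A later correlation would not undo a choice of regions already made in that way.

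Third, a reader might infer that rehabilitation doctors have the last word, or that unblinded therapists read the scans. Neither is stated. The two final doctors are undefined, and sharing a discipline does not make two people the same. If reading fMRI counts as outcome assessment, the blinding section already requires blinded readers and excludes the therapist. This reply stands, and it reduces the blinding limb to a request for clarification.

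Finally, fMRI is a secondary indicator and the Discussion calls the trial exploratory. That limits the weight of the point, but the measure carries one of only two objectives.

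**Conclusion.** The concern holds for the interpretation of the fMRI result. The plan has the final interpretation agreed after an analysis that includes the clinical symptoms, and the article gives no numerical analysis for the pain-brain relation it wants to test. The conclusion for objective 2 can therefore be drawn toward regions that fit the observed symptoms. The direction is toward an apparent link between pain relief and brain change. The size cannot be computed from the document.

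The computed group comparison and the clinical outcomes are not affected. On blinding, the finding is only that the text does not say whether the rule on therapists covers the MRI readers.

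This rests on two assumptions: that the agreed interpretation feeds the reported mechanistic conclusion, which is the evident purpose of the step, and that no fuller document fixes a different order of reading. The change should be made, since it replaces a stated procedure with a less biased one at little cost.

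**What to change.** Revise the section MRI data analysis as follows:

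- The two radiologists interpret and lock the ALFF group result with the arms coded A and B and without access to SF-MPQ, CMSS, SAS or SDS scores.
- The two doctors who agree the final interpretation are defined as these radiologists.
- The pain-brain relation is obtained by a separate numerical correlation of ALFF change with score change, stated in Statistical analysis. The score, the rule for choosing regions and the handling of treatment arm are fixed beforehand.
- Rehabilitation doctors may add clinical context only after the lock, and only if they treated no participant.
- The reference to clinical symptoms is removed from the reading step.

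Add one sentence to the blinding section stating that its rule covers everyone who reads or interprets the MRI results.

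The cost is protocol wording and a changed order of work. No extra staff or scans are needed, and the data for the correlation are already scheduled. The one small drawback is that clinical context comes in later.

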### Statistical analysis

Clinical and MRI outcomes will be obtained in this study. Among these outcomes, results from participants for both MRI scans and two clinical evaluations will be included in the results analysis; otherwise they will be considered data from drop-outs. Note that all participants in the experiment will receive our instructions before participating.

Statistical analysis of the clinical outcomes will be accomplished using the SPSS 22.0 statistical software. All tests will be bilateral, and *p* < 0.05 will be considered statistically significant.

Demographic characteristics and baseline information for all participants will be analysed statistically. For continuous data, independent sample *t* tests or Wilcoxon rank sum tests will be applied for analysis with data represented as mean ± standard deviation. If dichotomous data occur, we will use the chi-square test or the Friedman test and represent the data as percentiles.

For post-test results, the paired *t* test or Wilcoxon signed rank test will be employed for continuous data within the group. Conversely, the chi-square test or Fisher’s exact test will be applied for two-part data to compare the differences before and after treatment. For different intervention methods, independent sample *t* tests will be conducted to identify whether the intervention methods show differences for the relief of PDM.

The statistical comparison of MRI data will be conducted in different ways. With the use of the 3.0 T Siemens Magnetom Verio MRI system, each subject will produce two resting state scans. The data processing assistant for resting state fMRI (DPARSF 4.4) software package will be used to process MRI data on the MATLAB 2015b platform and obtain the ALFF values. The mean value of the amplitude of all frequency points within 0.01–0.08 Hz will be calculated; that is, the intensity of the BOLD signal changes will be calculated to obtain the brain map of the statistical parameter of amplitude, which will be used to describe the spontaneous activity of the voxel [23]. SPM12 software will be employed to perform two-sample *t* tests on the two groups of statistical brain maps. The final results will be superimposed on standard avg152 T1 images for display. Finally, the statistical difference of low-frequency amplitudes in the resting state between the two groups will be obtained, and *p* < 0.05 will be considered to indicate a significant statistical difference.

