#### Termination criteria

The criteria for termination of subjects with PDM are as follows:
Subjects taking other forms of pain relief, such as extra pain relievers, during the rESWT treatment period of this trialSerious AEs (SAEs)Surgery or hospitalisation for an accident or other diseasesParticipant request

A reminder will be sent the day before the appointment to ensure participant retention and adherence.

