### Interventions

The time of interventions will be within the first 48 h of the menstrual period (Fig. 2). Trained and qualified practitioners from the Ministry of Health of the People’s Republic of China will perform real and sham rESWT therapy on the participants. Before the intervention, the myofascial trigger points in the abdominal muscles (Fig. 3) will be clinically located by the clinician, and ultrasound coupling gel will be applied on the lower abdominal skin surface (Fig. 2). In the real rESWT group, therapists will use radial shock wave devices based on previous experience to apply 5000 impulses of radial shock waves with a pressure of 1.5 bar at a rate of 10–14 impulses per second for each participant (STORZ MEDICAL AG, MASTERPULS® MP100, C15, diameter 15 mm, Switzerland) (Fig. 4 and Table 2) [9, 10]. Patients in the sham therapy control group will receive placebo intervention with the same sound but no energy input [17]. Moreover, any other treatment to improve menstrual pain will be restricted in both the real and sham rESWT groups during the trial.

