### Outcome measurements

#### Primary outcomes

##### SF-MPQ

The primary outcome will be the change in the short form of the McGill Pain Questionnaire (SF-MPQ) score (Table 1). The SF-MPQ is a scale composed of a pain rating index, a visual analogue scale and existing pain intensity to measure pain intensity. The pain rating index consists of 11 sensory and 4 emotional pain descriptors, all of which are rated from 0 to 3 points to indicate the different degrees of no, mild, medium, or severe pain, respectively. This index is a sensitive and reliable pain evaluation method widely used in the assessment of dysmenorrhoea [18].

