### Sample size calculation

The smallest significant differences in clinical treatment are considered to assess the effects of different treatments. SAS 9.4 software was used to design the two groups with better efficacy. The optimal value was defined as 15%. According to previous research results, the effectiveness proportion of shock wave treatment for primary dysmenorrhea is known to be 0.8 [9, 10]. The control group for this experiment was the sham shock wave treatment group. Through previous practice observation, we determined the effectiveness of the control group proportion to be 0.45. The estimated sample size was 30 individuals (15 in each group) to meet the 80% statistical value [21] and the 5% significance level. Considering a 20% drop-out rate, the sample size was finally determined to be 36 participants (18 per group).

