### Security

AEs will be recorded during each operation. The following conditions are defined as SAEs: 1) aggravated illness requiring hospitalisation; 2) disability; and 3) other major medical events. In the event of an SAE, the lead investigator will report to the sponsor within 24 days, and the investigator will intervene as a third party to evaluate whether the AEs are connected to the intervention. If necessary, the appropriate medical services should be provided when the victim asks for compensation. Participants will be withdrawn if the AEs are too severe for them to continue with the trial. However, participants need not withdraw if the AE is unrelated to the intervention or is not a SAE, with respect to the individual wishes of the participants.

Given the safety of rESWT, no safe end point will be predefined because this is considered impossible. However, all AEs will be documented as evidence for safety assessment. Meanwhile, a meaningful number of adverse reactions will be observed.

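### The both-scans rule removes randomised participants from the SF-MPQ and CMSS comparison, which costs precision and, combined with termination for analgesic use, creates a risk of bias of unknown size and direction

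*Protocol article*

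**What the plan says.** The Statistical analysis section begins "Clinical and MRI outcomes will be obtained in this study. Among these outcomes", and then limits the analysis: "results from participants for both MRI scans and two clinical evaluations will be included in the results analysis; otherwise they will be considered data". Anyone else counts as a drop-out. The rule therefore covers the clinical scales and is not confined to imaging.

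The scales carry the primary comparison. "The primary outcome will be the change in the short form of the McGill Pain Questionnaire (SF-MPQ) score", and CMSS also stands under Primary outcomes. The arms are compared as follows: "For different intervention methods, independent sample *t* tests will be conducted to identify whether the intervention methods show differences for the relief of PDM". fMRI change is named in the abstract as a secondary indicator.

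Table 1 (Design) puts SF-MPQ and CMSS in the same columns as the two MRI scans, with allocation in the treatment column between them. Table 2 gives a single treatment session.

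Three other places bear on who reaches the second visit. Termination criteria lists "Subjects taking other forms of pain relief, such as extra pain relievers, during the rESWT treatment period". Interventions says that "any other treatment to improve menstrual pain will be restricted in both the real and sham rESWT groups during the trial". Security adds "Participants will be withdrawn if the AEs are too severe for them to continue with the trial". Sample size calculation allows for 20% drop-out.

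The article names no all-randomised analysis, no method for missing scores and no collection of scores after termination.

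**The concern.** A pain questionnaire needs no scan to be valid. Under this rule a participant who was randomised, treated and fully assessed on SF-MPQ and CMSS leaves the primary comparison if the second scan was refused, failed or was unusable. That is an avoidable loss.

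The second issue is selection. The primary outcome is pain, and taking a pain reliever is plausibly a sign of poor response. If termination for that reason leads to a missed second visit, the rule turns it into exclusion from the analysis. The arms being compared would then no longer be the arms that were randomised, and the difference could be distorted. Treatment is one session, so termination after it changes no exposure and only removes data.

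**Working it through.** **1. Does the exclusion act after randomisation?** Table 1 runs: first scan with questionnaires, then allocation and treatment, then second scan with questionnaires. The first-visit requirement is met or failed before allocation. Only the second-visit requirement removes randomised participants.

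**2. The plan's own figures.** 30 x 1.2 = 36, which is the stated total. If 20% are lost, 36 x 0.8 = 28.8, so about 29 are analysed (about 14 per group). If all were kept, the standard error would be smaller by a factor of sqrt(28.8/36) = 0.89. This is an upper limit on the gain, because not every lost participant has a recoverable score.

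The planning rates are 0.80 for rESWT ("the effectiveness proportion of shock wave treatment for primary dysmenorrhea is known to be 0.8") and 0.45 for sham. On these, two-sided 5% power for two proportions is about 0.48 at 14, 0.51 at 15 and 0.59 at 18 per group. The stated 15 per group for 80% power is not reproduced: [1.96 x sqrt(2 x 0.625 x 0.375) + 0.8416 x sqrt(0.16 + 0.2475)]^2 / 0.35^2 = 28.8, i.e. 29 per group. That is a separate matter and this point does not rest on it.

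**3. Illustration on a pain score (all inputs assumed).** Scale 0-10; baseline mean 6, SD 1.5; residual SD of change 2; mean change -1 on sham and -2.5 on rESWT, so the true difference is -1.5. A share q of those with post-treatment pain above 6 is excluded, by the same rule in both arms.

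- Post-treatment SD = sqrt(1.5^2 + 2^2) = 2.5; means 5.0 (sham) and 3.5 (rESWT).
- Standardised cut-off a = (6 - mean)/2.5 = 0.4 (sham) and 1.0 (rESWT). The share above 6 is 0.345 and 0.159.
- Slope of change on post-treatment pain = 4/6.25 = 0.64.
- Shift of the retained mean change = -0.64 x 2.5 x q x phi(a) / [1 - q(1 - Phi(a))], with phi(0.4) = 0.368 and phi(1.0) = 0.242.

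| q | Loss, sham / rESWT | Shift, sham / rESWT | Difference in those retained |
|---|---|---|---|
| 50% | 17% / 8% | -0.356 / -0.210 | -1.35 |
| 70% | 24% / 11% | -0.544 / -0.305 | -1.26 |
| 100% | 34% / 16% | -0.899 / -0.460 | -1.06 |

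Simulation of 20,000 trials with 18 per group gave -1.36, -1.26 and -1.06. The 100% row loses about 25% overall, more than the plan's 20%, so only the first two rows lie within its own expectation: shrinkage of about 10% and 16%. For scale, the standard error at 15 per group is sqrt(2 x 4/15) = 0.73.

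**4. Direction, on the planning rates.** If a share q of non-responders is excluded and responders are kept, the observed rate is p/[p + (1 - p)(1 - q)].

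- q = 50% in both arms: 0.889 vs 0.621, difference 0.27 against a true 0.35; overall loss (0.10 + 0.275)/2 = 19%.
- q = 10% rESWT, 40% sham: 0.816 vs 0.577, difference 0.24.
- No true effect (0.45 in both arms), equal q: no bias. With q = 40% vs 20%: 0.577 - 0.506 = 0.07, a spurious difference.

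The bias can therefore shrink a real difference or create a false one, depending on exclusion shares that the documents do not give.

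**5. Bounds.** Suppose 12/15 vs 7/15 completers respond (difference 0.33) and 3 per arm are missing. The all-randomised difference then lies between 12/18 - 10/18 = 0.11 and 15/18 - 7/18 = 0.44.

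**6. Would imputation from baseline repair it?** In the model of step 3, imputing by arm from baseline gives about -1.35, -1.23 and -0.91. That is no better than completers, and worse in the extreme case.

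**The case against.** A reader might infer that analgesic users are excluded by rule, or that the sham participants with the worst pain leave the analysis. The documents do not say either. Termination criteria ends the subject's participation; exclusion follows only if the second scan or evaluation is then missing. This is an inference from two sections read together.

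The route may also be narrow. The treatment period is not defined in the article, there is one session, the stated interest is an immediate effect, and the case procedure figure is not available, so the time from treatment to second assessment is unknown. Analgesic use before the session cannot reflect response to it.

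The scan route may be small too. Scans and questionnaires share a visit, so someone who misses it probably lacks both, and nothing suggests that failed scans depend on pain or arm. Every input to the pain-score illustration is assumed, and with no true effect and the same exclusion rule in both arms that model shows no bias. The Discussion calls the trial exploratory.

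All of this limits how strongly the point can be put. It does not remove it. The rule is stated outright for clinical outcomes, so an unseen analysis plan or a condensed article does not explain it, and nothing elsewhere in the article offsets it.

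**Conclusion.** The point holds as a post-randomisation exclusion from the primary comparison. The certain part is that valid SF-MPQ and CMSS scores are discarded when only the second scan is lacking, at a cost in precision. The conditional part is a risk of bias, because one exit route is related to pain and may be used unequally between arms.

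The stronger claim, that the randomised comparison is already broken or is biased in a known direction, is not supported: the documents give no exclusion rates by arm or outcome. The shrinkage from -1.5 to about -1.35 to -1.26 rests wholly on the assumed scale, SDs, effect, threshold and exclusion shares, and unequal exclusion could instead produce a spurious difference. The rule should still be changed, because it decides who enters the main efficacy comparison and the change is cheap.

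**What to change.** In Statistical analysis:

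- Analyse SF-MPQ and CMSS in all randomised participants in their assigned group, using every available post-treatment score whatever the MRI status. State that this comparison is made regardless of analgesic use.
- Confine the both-scans requirement to the fMRI analysis, and report the completer analysis of the clinical scales as secondary.
- Keep collecting the post-treatment questionnaires after termination, recording any analgesic intake and its time.
- For scores still missing, do not rely on imputation from baseline alone. Add a sensitivity analysis in which missingness may depend on outcome, such as delta-adjusted imputation or best- and worst-case bounds.
- Add a sensitivity analysis that treats analgesic users differently, for example counting them as non-responders, with response defined in advance.

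The cost is revised analysis wording and one set of questionnaires for those who miss the second scan. There is one small downside: scores taken after other pain relief include its effect. The completer analysis cannot isolate that, because it carries the same selection; hence the last item. No view is taken on the clinical termination rule itself.
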